### 2.6. ACT for Inpatients (ACT-IN) Protocol

The treatment protocols used in the Gaudiano and Herbert [44] and Bach and Hayes [42] studies were adapted for the current study. ACT-IN has multiple components that are theorized to target the mechanisms of mindfulness, acceptance, and values in order to improve symptoms, functioning, and rehospitalization rates following discharge (see Figure 3). Average length of hospital stay for patients with SSD at our recruitment site is about one week. The number of ACT-IN sessions varies based on the length of hospital stay as done in our pilot work [44]. The intervention uses a rolling/open format so that patients can start and stop sessions as their length of stay dictates, with a target of three individual and three group sessions per week. In each session, various mindfulness and acceptance exercises as described by Hayes et al. [34] are introduced to help patients decrease avoidance or struggle with internal experiences, including psychotic symptoms, which cause functional impairment.

We made several modifications to ACT-IN to improve its potentially implementability and effectiveness in routine hospital settings. For example, we included both individual and group sessions to provide a greater “dose” of ACT compared with previous studies that were individual only. This also allows greater consistency of treatment during hospitalization and acknowledges the fact that group therapy is a major component of psychosocial treatment on most inpatient units. We considered administering ACT-IN in a group format alone to maximize the potential for easy uptake in routine hospital settings. However, we concluded that less experienced clinicians may not be able to provide a sufficient amount of treatment to achieve optimal clinical improvement. The combination of individual and group sessions balances these concerns and recognizes that both formats are used to provide brief psychosocial intervention on many units today. In addition, we developed training procedures and a treatment protocol designed for providers who may not have had previous experience with ACT or other evidence-based psychosocial approaches for psychosis. The ACT-IN treatment manual is presented in a simplified format with more structure and examples than other manuals to facilitate delivery by less experienced clinicians. Group sessions are designed to be conducted in an open format so that patients can participate in sessions as their length of stay dictates. In addition, the treatment is designed to be applicable to patients with a wider range of diagnoses (e.g., primary psychotic and psychotic mood disorders) and presentations (e.g., those with lower cognitive functioning and comorbid conditions) given the higher levels of complexity and acuity found in patients treated on inpatient units (as described below).

The final content of ACT-IN will be developed based on the lessons learned during the current project. However, what follows represents our initial plans for the intervention. The first ACT-IN individual session with the patient is focused on introducing the ACT model, establishing rapport, collecting history of illness to highlight the pernicious role that avoidance plays in exacerbating symptoms, and identifying values-consistent behavioral goals that the patient will work on during treatment. Subsequent individual and group sessions adhere to the following general format.

First, the ACT model is explained. Then, the therapist guides patients through an exploration of previous attempts to cope with symptoms, the successfulness or unsuccessfulness of these strategies, and their consequences. Unhelpful attempts to avoid or struggle with these symptoms are explored in the context of their “workability” to achieve a valued goal. The therapist highlights attempts by patients to avoid or struggle with symptoms that paradoxically seem to cause increased distress, intensity, or impairment. The therapist then notes that it is important not just to consider the effects of the symptoms themselves, but also how one responds to them.

Next, patients are taught various mindfulness and acceptance strategies to nonjudgmentally observe and cognitively defuse from their thoughts, and to notice that they can have symptoms without acting on them or trying to change them. Intensive meditation practices are generally contraindicated for patients with acute psychosis [77]. Mindfulness exercises are modified to be appropriate for this patient population by making them “eyes open”, briefer in duration, and focused on bringing nonjudgmental awareness to external stimuli in the present moment (e.g., eating, walking). For example, the therapist leads the patient/group in a brief (5–10 min) mindfulness exercise in which individuals are instructed to eat a piece of food (e.g., a raisin) or to walk around quietly in a mindful fashion while staying present. During this mindfulness activity, patients are instructed to notice their various sensory experiences one at a time (e.g., noticing how their foot feels when contacting the ground repeatedly).

Furthermore, the concept of values is introduced and explored during sessions. Values are described as the things that give a person’s life meaning and purpose and are individually chosen. The therapist clarifies possible values that may be relevant to each patient, including family, romantic relationships, work, leisure, and health. The values clarification discussion involves developing a more in-depth description and elaboration of valued areas based on a patient’s personal life situations. Discrepancies between the person’s valued area and his/her daily actions are highlighted along with the distress this tends to cause. The therapist suggests that being more consistent with values in one’s daily actions can lead to a more fulfilling and healthy life. Specific behavioral goals are then discussed and a written plan for implementing them after the session is developed in collaboration with the patient.

Sessions end with a discussion of “take home” messages and ways of implementing the strategies learned in between sessions. Following the same basic format as described above, different ACT “themes” are rotated across sessions and include: values clarification, mindfulness, acceptance, and cognitive defusion. In each session, various stories/metaphors and experiential exercises are implemented relevant to each ACT theme. Patients are encouraged to practice exercises and to work toward valued goals between sessions. For an extended discussion of ACT for psychosis strategies see Gaudiano (2013) [78].

### 2.7. Study Therapists

We will use staff typically employed on hospital units as study therapists, including social workers, master’s level counselors, nurses, and occupational therapists. Therapists will be trained to: (a) understand and learn to perform the treatment protocols consistently across patients and (b) avoid using techniques that are not part of the treatment. Educational materials are drawn from the treatment manual on the conceptualization, components, and delivery of the intervention. The teaching materials include video role plays to demonstrate appropriate vs. incorrect interventions, plus strategies to manage patients who may have difficulty using techniques. A didactic training workshop is used, in which instructors present the material, answer questions, and role-play various strategies and situations. Following the didactic training, study therapists participate in “mock” sessions in which they deliver intervention content with study staff acting as confederates. These sessions are recorded and assessed for fidelity and competency. Ongoing supervision will be provided to therapists throughout the study to problem solve issues and to prevent protocol “drift”. Remedial training and practice will be provided to therapists who do not maintain acceptable fidelity.

### 2.8. Treatment Fidelity

An initial version of the ACT-IN fidelity scale was developed to assess therapists’ adherence to the protocol and skill in delivering each treatment component in group and individual formats, as well as in developing a positive therapeutic environment (i.e., empathy, warmth, flexibility). The goal was to create a usable scale that could be employed in teaching ACT to staff, as well as for evaluating fidelity to ACT. Items were generated based on the treatment manuals and existing fidelity scales used in previous studies [79,80]. Sessions will be recorded and a random selection of sessions will be coded for fidelity by research staff trained to initial interrater reliability.

### 2.9. Assessments

Assessments will be conducted shortly after hospital admission (baseline), at hospital discharge (or shortly thereafter for unexpected discharges), and 4 months post-discharge (as done in the initial ACT inpatient studies). At admission, clinical interviews will assess the week immediately preceding hospitalization, the discharge assessment will assess current severity/functioning (past 24 h), and the follow-up assessment will assess the previous week. We will assess diagnosis, psychiatric symptom severity including psychosis, psychosocial functioning and quality of life, treatment adherence and utilization (including rehospitalization rates at follow-up), treatment satisfaction and acceptability, and the proposed mechanisms of ACT-IN (mindfulness, acceptance, values). Severity of positive and negative symptoms will be assessed using the relevant subscales from the BPRS, which have demonstrated reliability and validity for this purpose [81]. A list of measures with a brief description of each is provided in Table 1.

### 2.10. Assessors

Assessors will be blind to treatment assignment. All assessors will receive comprehensive training including: (a) review of assessment manuals and training recordings, (b) supervised role-playing, and (c) practice interviews. We will follow training procedures for the BPRS developed by Ventura et al. [82] involving demonstration of reliability via ratings of 6 standardized clinical interview recordings. Prior to administering study assessments, all assessors will be required to achieve adequate reliability (ICC ≥ 0.80) with other trained raters, and then undergo periodic checks to prevent “drift”. During the study, all interviews will be recorded and periodically checked for accuracy. Should any interviewer inaccuracy or drift be detected, further training will be provided.

### 2.11. Retention Efforts

Our goal will be to achieve <20% attrition over the course of the study. However, we will assess whether attrition is higher than expected and use this information to determine feasibility and sample size needed for a future large-scale clinical trial. Subjects will be compensated for completing assessments ($25 each for the admission and discharge assessments, and $50 for the follow-up assessment). Assessors will phone patients periodically during follow-up to maintain contact and update information. Cab rides/bus passes will be provided for subjects unable to transport themselves to our center for their follow-ups. We will attempt to continue to collect assessment data even if patients withdraw from the study.

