Gaudiano and Herbert [44] conducted a study that improved on Bach and Hayes’ methodology by adding an established measure of symptom severity (the Brief Psychiatric Rating Scale [45]) and using an enhanced TAU condition that controlled for therapist contact time. Among a sample of 40 patients with SSD, they found that an average of 3 individual therapy sessions of ACT over 1 week of inpatient hospitalization resulted in greater improvement in clinically significant symptom changes (especially mood symptoms), disability related to illness, and distress related to psychotic symptoms by hospital discharge. A survival analysis controlling for baseline symptom severity showed that ACT produced a significantly longer time to rehospitalization at 4 month follow-up compared to TAU [46]. Furthermore, evidence was found to support the proposed mechanisms of action of ACT for psychosis. Changes in believability of psychotic symptoms mediated the effects of treatment condition on levels of distress about psychotic symptoms at hospital discharge [47]. In addition, changes in believability of psychotic symptoms mediated the effects of treatment condition on 4-month rehospitalization rates in an analysis of the combined datasets from the Bach and Hayes and Gaudiano and Herbert studies [46].

Thus, ACT is the only specific psychosocial treatment found to be feasible and efficacious for inpatients with psychosis with shorter hospital stays in the U.S. based on randomized clinical trials to date. However, both the Bach and Hayes [42] and Gaudiano and Herbert [44] studies provided brief treatment, lacked blind raters, and assessed a limited range of outcomes, especially post-hospitalization. In addition, these studies were conducted by ACT-trained research therapists using an individual-only therapy format without integration into the hospital unit milieu (i.e., group therapy and other interactions with unit staff), limiting the potential implementability of the intervention in routine inpatient settings. Not surprisingly, then, the uptake of ACT on inpatient units has been slow and inconsistent to date.

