Regarding treatment feasibility/acceptability, we will assess attrition rates and reasons for drop out. We also will assess levels of treatment acceptance and satisfaction (CSQ-8). Similar to other studies in this area [95,96], the primary outcome will be change on the BPRS total scale. Secondary outcomes will include symptom subgroups (e.g., positive, negative, mood), overall response rates (≥30% reduction [97] on BPRS), psychosocial functioning and quality of life, and rehospitalization rates. We also will examine potential predictors of outcomes to identify moderators and mediators that could be tested in subsequent research, including demographics, treatment adherence, and the proposed ACT-IN treatment mechanisms (AAQ-II, CAMS-R, VQ).

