**Psychiatric Symptoms**			
Brief Psychiatric Rating Scale (BPRS) [45,82]	Psychiatric symptoms	Interviewer	BL,DC,4
Clinical Outcomes in Routine Evaluation (CORE) [83]	Psychiatric symptoms	Self-Report	BL,DC,4

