**Treatment Adherence/Utilization**			
Brief Adherence Rating Scale (BARS) [87]	Medication adherence	Interviewer	4
Treatment History Interview-4 (THI-4) [88]	Treatment utilization	Interviewer	4

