**Acceptability/Satisfaction**			
Client Satisfaction Questionnaire-8 (CSQ-8) [91]	Treatment satisfaction	Self-report	DC
Qualitative Post-Treatment Interview	Treatment satisfaction	Interview	DC

Note: BL = Baseline, DC = Discharge, 4 = 4 Month Follow-up.

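### The assessors who must stay blind are also given the follow-up phone calls, an avoidable route to disclosure of the arm before the 4-month ratings

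*Protocol article*

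**What the plan says.** Section 2.10 sets the requirement: "Assessors will be blind to treatment assignment". It also describes rater training, a reliability threshold, and recording of interviews with periodic accuracy checks.

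Section 2.11, on keeping patients in the study, says: "Assessors will phone patients periodically during follow-up to maintain contact and update information".

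Section 3 states that "the primary outcome will be change on the BPRS total scale". Table 1 lists the BPRS and the Heinrichs scale as interviewer-administered at baseline, discharge and 4 months. It lists the THI-4, on treatment utilization, as interviewer-administered at 4 months. It also lists a "Qualitative Post-Treatment Interview" at discharge, with treatment satisfaction as its construct, and does not name who conducts it.

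Section 1, reviewing the two previous inpatient ACT trials, counts among their limitations that they "lacked blind raters".

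**The concern.** The BPRS and the Heinrichs scale depend on the rater's judgement, so knowing the arm can influence the score. The patients are not blind. A rater has to meet the patient in order to rate, and some risk of disclosure in that meeting cannot be avoided. The retention calls are different: nothing about rating requires the rater to make them. Giving them to assessors adds repeated conversations with patients in the months before the last rating.

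At stake is the credibility of the 4-month BPRS and quality-of-life comparison. The article treats unblinded rating as a weakness of the previous trials, so blind rating is one of the improvements this trial offers. Section 3 also makes specifying procedures for a later full-scale trial part of the primary objective, so a weak task allocation could be carried forward.

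**Working it through.** No arithmetic settles this point. The check is to set the sections side by side and separate what they establish from what they leave open.

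**Established by the text**

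1. The role that must be blind is the assessor (2.10).
2. The role that phones patients periodically during follow-up is the assessor (2.11).
3. Follow-up runs from discharge to 4 months (2.9), so the calls precede the 4-month ratings and come after the discharge ratings.
4. The BPRS and the Heinrichs scale are rated by interview at 4 months (Table 1), and change on the BPRS total is the primary outcome (Section 3).
5. Both arms receive a similar number of individual and group sessions, but eTAU contains no ACT-IN content (2.5.1). Attending sessions therefore does not reveal the arm; describing their content can.
6. ACT-IN content is distinctive. Sections 2.5.2 and 2.6 describe metaphors and stories meant to be memorable, mindful eating and walking, and written plans built on the patient's values.

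Items 1 to 4 place an avoidable contact between a blind role and an unblinded patient before a judgement rating. Items 5 and 6 show that a patient's remark about session content could reveal the arm.

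**Left open by the text**

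- Whether the person who calls a given patient also rates that patient. Section 2.11 names a role only.
- Whether the calls touch on treatment. Their stated purpose is keeping contact and updating information.
- Who conducts the discharge qualitative interview. Table 1 gives its method as an interview and names no one.
- The order of instruments within a visit, including whether the 4-month BPRS comes before or after the THI-4.

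**Which ratings are exposed.** The calls cannot affect the discharge BPRS. Of the two post-baseline time points (discharge and 4 months), only the second is exposed through the calls.

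**Size.** Any bias would be the share of ratings made with knowledge of the arm multiplied by the average shift that this knowledge causes. The article gives neither. With purely assumed ranges of 10% to 50% for the share and 0.2 to 0.4 SD for the shift, the product runs from 0.10 × 0.2 = 0.02 SD to 0.50 × 0.4 = 0.20 SD. A tenfold range built on two assumptions shows only that the size is unknown.

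**The case against.** The strongest reply is that the calls are narrow in purpose and the arms are hard to tell apart in casual talk. eTAU includes cognitive-behavioral skills, symptom-coping and relaxation groups plus individual supportive therapy, so a patient who mentions groups or coping skills gives nothing away. Only ACT-specific content would, and a call to update contact details does not ask for it. The trial is an unpowered pilot whose primary objective is feasibility and acceptability, and its outcome models are called exploratory. Interviews are recorded and checked. Safeguards such as call scripts or instructions to patients may be in the full protocol, which is not shown.

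Most of this stands and keeps the point modest. The absence of such safeguards from an article is not itself a fault. What remains is the task allocation that the article states. Recording and accuracy checks limit rating drift but do not protect the blind.

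Three stronger readings are tempting and are not supported:

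- A reader might infer that the discharge qualitative interview unblinds the raters. It could do so only if a BPRS rater conducts or sees it, and the article does not say so. It shares the discharge time point with the BPRS, with no stated order, so it cannot be placed after the discharge rating either.
- A reader might infer that Sections 2.10 and 2.11 contradict each other. They do not: an assessor can phone a patient and remain blind.
- A reader might take the top of the assumed range, 0.20 SD, as the likely bias because it matches the article's small effect (f = 0.10; for two equal groups d = 2f = 0.2). It is the extreme corner of two assumed ranges. Section 3 expects medium to large BPRS effects (f = 0.25 to 0.40, so d = 0.5 to 0.8).

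**Conclusion.** The point holds as a modest, avoidable risk to the blind at the 4-month visit. It rests on the stated assignment of follow-up calls to the role that must be blind, and on the interviewer-rated outcomes that follow those calls. It assumes that at least some assessors who call a patient also rate that patient, or share what they hear with the person who does; the article neither states nor excludes this. The size cannot be quantified from the document, and nothing in it shows that bias has occurred or will occur. The discharge BPRS is not affected by the calls. Correction is worthwhile because it is cheap and because Section 4 says that the pilot RCT is recruiting and that procedural changes are expected.

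**What to change.** 1. Have the retention calls made by research staff who do not rate that patient. Sections 2.3 and 2.8 mention research team members who recruit and who code fidelity; the article does not say whether they also rate, so this needs checking locally.
2. If staffing does not allow this, give the callers a contact-only script that opens with a reminder not to discuss treatment sessions.
3. At 4 months, complete the BPRS and quality-of-life ratings before the THI-4. The article does not show that the THI-4 elicits arm-specific content, so this is a precaution.
4. Record the assessor's guess of arm at the 4-month rating, so that the pilot yields some evidence on how well the blind held.
5. State that BPRS raters do not conduct the discharge qualitative interview.

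The cost is a reallocation of tasks among existing staff, one added form item and a sentence or two of text. Sample, treatment and analysis are unchanged. The downside is some loss of continuity between assessor and patient, which could slightly affect retention, where the article aims for attrition below 20%.

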## 3. Sample Size and Data Analysis Considerations

As recommended for pilot projects [92], we did not power the study for effect sizes at certain *p* values due to the large confidence intervals around effects in smaller samples. Instead, the primary objective of the REACH treatment development project is to establish acceptability/feasibility and specify study procedures in preparation for a *future* fully-powered clinical trial [92]. However, a preliminary power analysis is provided below as a guide for a future large-scale clinical trial should the pilot project prove successful. In order to have an 80% power to detect group differences at a two-tailed alpha level of .05 over 3 time points, a small treatment effect (f = 0.10) would require a total *n* = 526, a medium effect (f = 0.25) would require *n* = 86, and a large effect (f = 0.40) would require only n = 36. Clinically meaningful effect sizes on symptom outcomes (BPRS) are expected to be medium to large in magnitude and should place future sample size requirements in a feasible range. We should be able to gauge relevant treatment parameters with an open trial sample of 20 and a pilot RCT sample of 50. This will require recruitment of approximately 3–4 patients per month into study, which is feasible based on the admission rate at our study site and the recruitment rate achieved by the investigators in their previous studies.

We will examine effect size standard errors, confidence intervals, and clinically meaningful statistics (e.g., “number needed to treat”) as recommended for treatment development trials [93]. Furthermore, we will examine patterns of missing data and explore multiple methods for imputing data to determine consistency of results (maximum likelihood estimation, multiple imputation, and “worst case” scenario). If baseline differences are identified and associated with outcomes, these variables will be used as covariates in subsequent analyses. For example, history of illness (e.g., first episode versus chronic psychosis) may be important to examine due to its relationship with outcome in schizophrenia [94].

Regarding treatment feasibility/acceptability, we will assess attrition rates and reasons for drop out. We also will assess levels of treatment acceptance and satisfaction (CSQ-8). Similar to other studies in this area [95,96], the primary outcome will be change on the BPRS total scale. Secondary outcomes will include symptom subgroups (e.g., positive, negative, mood), overall response rates (≥30% reduction [97] on BPRS), psychosocial functioning and quality of life, and rehospitalization rates. We also will examine potential predictors of outcomes to identify moderators and mediators that could be tested in subsequent research, including demographics, treatment adherence, and the proposed ACT-IN treatment mechanisms (AAQ-II, CAMS-R, VQ).

Given all patients will be receiving appropriate pharmacotherapy as part of their hospital stay, we expect that both groups will show significant improvement in symptom severity by discharge. However, we also are interested in examining whether ACT provides certain advantages in terms of its impact on nonpsychotic symptoms (e.g., mood symptoms) or other outcomes (e.g., psychosocial functioning) compared with eTAU. Consistent with the analyses we would plan to conduct in a future full-scale RCT, we will generate multilevel linear models in a preliminary fashion to examine whether treatment condition, time, and the treatment condition X time interaction predicts change in outcomes (symptoms, functioning, rehospitalization) and proposed mechanisms [98]. These exploratory analyses will follow the intent-to-treat principle (i.e., all patients randomized to treatment). Differences in median days to hospitalization between conditions, log-rank test, and preliminary Cox proportional hazards models will be used to understand treatment effects on time to re-hospitalization during follow-up. In addition, the potential magnitude of the indirect effect of condition on outcomes will be explored in a preliminary fashion by testing between-condition differences in mechanisms targeted by the intervention (path ‘a’) (e.g., mindfulness) and determining whether group differences (path ‘b’) are related to outcomes. The product of path coefficients will provide an estimate of the mediation effect and confidence intervals [99]. We acknowledge we will be underpowered for formal mediation testing. However, the partitioning of variance should provide interpretive guidance regarding the effects of ACT-IN mechanisms when assessing symptomatic outcomes.

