### 2.4. Randomization

Patients will be assigned to conditions in the pilot RCT in a 1:1 ratio, with 2 stratification variables: gender and diagnosis (primary psychotic disorder vs. psychotic mood disorder). For example, gender is a theoretically important stratification variable because women with schizophrenia tend to have better premorbid functioning, a later age of onset, a different symptom profile, and a better course of illness compared with male patients [50]. Randomization will be conducted by a computer program with no research staff aware of assignments in advance.

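### Covariates enter only if they look imbalanced at baseline and relate to outcome; a fixed set, led by the two stratification factors, would serve the pilot's estimates better

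*Protocol article*

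**What the plan says.** Section 3 (Sample Size and Data Analysis Considerations) sets the covariate rule: "If baseline differences are identified and associated with outcomes, these variables will be used as covariates in subsequent analyses". It gives no threshold for a difference or an association and no list of candidates. History of illness (first episode versus chronic) is offered as an example, on the ground that it relates to outcome.

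Section 2.4 (Randomization) allocates 1:1, stratified by gender and by diagnosis (primary psychotic versus psychotic mood disorder). It justifies gender on prognostic grounds: "women with schizophrenia tend to have better premorbid functioning, a later age of onset, a different symptom profile, and a better course of illness".

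Section 3 describes the main analysis as "multilevel linear models in a preliminary fashion to examine whether treatment condition, time, and the treatment condition X time interaction predicts change in outcomes". It names no covariates or strata there. On the status of the models it says "These exploratory analyses will follow the intent-to-treat principle", and it introduces them with "Consistent with the analyses we would plan to conduct in a future full-scale RCT". The same section says that the pilot was not powered for given p values, that its primary objective is acceptability and feasibility, and that effect-size standard errors and confidence intervals will be examined.

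**The concern.** A covariate earns its place by its relation to outcome, not by a chance difference between arms. The written rule requires both, and this has three consequences.

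- The adjusted model cannot be known until outcome data have been seen.
- A strongly prognostic factor that happens to be balanced is left out, although adjusting for it would sharpen the estimate.
- Gender and diagnosis are kept balanced by the randomisation, so they will seldom meet the first condition. The protocol relies on prognostic value to choose gender as a stratification factor, then applies a rule under which it will rarely be used in the analysis.

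At stake are the width and reproducibility of the effect-size intervals from 50 patients. Because the models are described as those intended for a full-scale trial, the rule could also be carried forward.

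**Working it through.** **The plan's own figures.** Section 3 gives a total n of 526, 86 and 36 for f = 0.10, 0.25 and 0.40 (80% power, two-sided 0.05, three time points), as a guide for a future trial. A repeated-measures between-group F test with λ = f²·N·3/(1 + 2ρ), df 1 and N − 2, and ρ = 0.5 (assumed; not stated) gives 526, 86 and 36 exactly. The point does not rest on an error in these figures.

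**Inputs.** From the documents: 50 patients, 1:1, so 25 per arm; two strata; BPRS at baseline, discharge and 4 months (Table 1). Assumed, because the documents give no value: R², the share of variance in BPRS change explained by the strata, and a standardised effect d.

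**Standard error.** With strata balanced by design but omitted from the model, the reported standard error is too large by 1/√(1 − R²):
- R² = 0: 1.00
- R² = 0.10: 1/√0.90 = 1.054
- R² = 0.20: 1/√0.80 = 1.118

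**Type I error without the strata** (large sample), 2·[1 − Φ(1.96/√(1 − R²))]:
- R² = 0: 0.050
- R² = 0.10: 0.039
- R² = 0.20: 0.028

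**Power at d = 0.5, 25 per arm**, noncentral t with noncentrality 0.5·√12.5/√(1 − R²):
- unadjusted: 0.5·√12.5 = 1.768, 48 df, 41%
- adjusted, R² = 0.10: 1.768/√0.90 = 1.863, 45 df, 45%
- adjusted, R² = 0.20: 1.768/√0.80 = 1.976, 45 df, 49%
- adjusted, R² = 0.02 to 0.05: 42% to 43%

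**Simulation of the written rule.** N = 50, stratified blocks of 4, four other covariates, p < 0.05 at both steps (all assumed), 0.6 SD effect. r is the correlation of each stratum with BPRS change; the other covariates have r = 0.2, or 0 in the first row.

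| r per stratum | type I, rule | type I, strata fixed | power, rule | power, strata fixed |
|---|---|---|---|---|
| 0 | 0.048 | 0.051 | 53.8% | 54.1% |
| 0.2 | 0.041 | 0.050 | 54.5% | 58.2% |
| 0.3 | 0.030 | 0.051 | 53.5% | 63.2% |
| 0.4 | 0.019 | 0.052 | 53.2% | 70.5% |

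If the two strata are independent, R² = 2r², so these rows are R² = 0, 0.08, 0.18 and 0.32. At r = 0.3 the rule's average model standard error was 0.282 against an empirical 0.252, a ratio of 1.12. Loosening the threshold to 0.2 left the type I error below 5% (0.047 with no prognostic covariates; 0.020 with strata and covariates at r = 0.3).

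**How the strata must enter.** The effect of interest is condition × time. In simulated complete-data trials (N = 50, three visits, random intercept), adding gender and diagnosis as main effects left the interaction estimate identical to rounding error and its standard error unchanged (ratio 1.0000). A gain appears only when the strata interact with time, or in an ANCOVA on follow-up.

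**The case against.** The strongest reply is that this is a pilot. It disclaims power, makes feasibility its main objective, and labels these models exploratory and preliminary. That stands: a loss of power or a departure from nominal error is not a failed promise here. The remaining harm is to the intervals the pilot does promise to examine, and to the analysis it is meant to rehearse.

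Second, a journal article may leave full model terms to an analysis plan. That also stands for the strata. Section 3 says which effects will be examined and does not say that other terms are excluded, so a reader who infers that the strata will certainly be left out goes beyond the text. The selection rule is different, because the article states it.

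Third, a reader might infer that the rule inflates false positives. The calculations do not support this: the error rate stayed at or below 5% in every scenario. The open wording would not stop an analyst from choosing covariates by the treatment result, but nothing in the document proposes that. Nor does the chance that at least one of 10, 15 or 20 independent variables differs at p < 0.05 (1 − 0.95^k = 40%, 54%, 64%) measure harm, since the rule also requires association with outcome.

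Fourth, a reader might expect a power gain near 20 points. A simulation with three prognostic covariates at r = 0.5, 0.3 and 0.3 gives 39% under the rule, 41% unadjusted and 59% with all three fixed. That rests on R² = 0.25 + 0.09 + 0.09 = 0.43, which no passage supports, and on covariates other than those named here.

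**Conclusion.** The rule is a poor one, and a better one costs little. Imbalance is the wrong trigger in a randomised comparison, and stratification makes it unlikely that the rule will admit the two factors the design itself treats as important. The consequence is modest and conservative: intervals that are somewhat too wide and a model that depends on the data.

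The size rests wholly on an assumed relation between the strata and BPRS change. With no relation there is no loss; at 10% to 20% of variance the standard error is overstated by about 5% to 12%, and prespecified adjustment would add about 4 to 8 points of power at d = 0.5. The selection rule carries the point. The absence of strata from the stated model is only weak support.

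**What to change.** In Section 3, replace the imbalance-triggered sentence with a fixed covariate set for the between-arm models: gender and diagnosis group and, if wanted, history of illness, included whatever imbalance is observed. State how they enter: as covariate × time terms in the multilevel model, or in an ANCOVA on the follow-up score with baseline BPRS. Main effects alone would not change the condition × time contrast. Report baseline imbalance descriptively, and keep any imbalance-based adjustment only as a labelled sensitivity analysis.

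The cost is a few degrees of freedom and a short change of wording. Gender and diagnosis group are already known at randomisation.
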